### Data management

Electronic device data will be collected from the Dexcom CGM using the Dexcom Clarity software. During the study, study-specific source documents will be maintained in locked file cabinets in locked rooms, and/or password protected databases via password protected computers in locked rooms. Post-study, study-specific source documents will be archived at a secure site at the University of Otago. Source documents will be retained for at least 10 years, then destroyed. Identifiable data will be converted to a de-identified form at the study site, at which point it is entered into electronic case report forms using the secure data platform REDCap (Research Electronic Data Capture). The data platform complies with international and national regulatory requirements for electronic data capture systems in the countries where it is used. Data entry will be limited to designated study staff trained and experienced in transcribing data for this purpose. The de-identified database will remain on securely held University servers for up to approximately 15 years.

### Statistical analysis

Statistical analysis will be performed using up-to-date specialist software (R or Stata). Analysis will follow the intention-to-treat principle, with all participants who commence the RCT phase included in the data set as randomised. Two-sided P-values will be reported, with an alpha of 0.05 considered statistically significant. The type 1 error for primary and secondary efficacy outcomes will be controlled using an ordered testing procedure where formal testing stops as soon as a non-significant result (p > = 0.05) is observed. Analysis of secondary exploratory outcomes will use the two-stage Benjamini-Hochberg method to control the false discovery rate.

Real-time CGM data will be collected in the run-in phase and week 10–12 of the RCT phase and used for calculation of baseline and follow-up CGM metrics, respectively. Participant CGM metrics will only be set to missing if less than 24 hours of data has been collected. The primary endpoint (TIR 3.9–10.0 mmol/L; 70- 180 mg/dL) will be calculated for each participant by dividing the number of CGM measures in target range, by total number of CGM values recorded. The overall treatment effect (primary outcome) will be determined by fitting an ordinary least squares linear regression model with percentage time in target glucose range at 12 weeks as the dependent variable and treatment group as the independent variable. The model will adjust for stratification variables (baseline use of metformin and use of SGLTi or GLP agonist) and percentage time in target glucose range during the last two weeks of run-in. This model will be used to calculate point estimate, 95% profile likelihood confidence intervals, and p values for the treatment group difference at follow-up. Continuous secondary endpoints (e.g CGM metrics, anthropometric, clinical and laboratory cardiovascular measures and PSQI) will follow the same approach as described for the primary efficacy endpoint.

Real-time CGM data will be collected daily during the entire continuation and extension study phases. This data will be pooled with data collected during the run-in and RCT phases and analyses undertaken using linear mixed-effects models. These models combine observed between-group and within-person treatment effects, and allow for changes over time to be estimated. Model fixed effects will include current treatment (Dexcom CGM or SMBG), time on study and time on intervention. Individual variation in glycaemic control at baseline and changes over time will be allowed for using random effects.

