## Methods

### Study design

This multi-centre, randomised controlled trial (RCT) of 80 participants will be conducted in Aotearoa New Zealand over a period of 14 weeks, including a 2-week run-in period for blinded CGM data to be collected from all participants. Following the 2-week run-in period, participants will be randomised 1:1 to either the rtCGM intervention arm (Dexcom G6 rtCGM system (Dexcom Inc., San Diego, CA)) or the control arm (SMBG) with a CareSens premier meter (i-SENS Inc., Seoul, Korea)) for a period of 12 weeks. The primary endpoint will be measured in the final two weeks of the RCT phase (week 10–12), with blinded rtCGM data collected from the control group and compared with unblinded rtCGM data from the intervention group. The 12-week RCT phase will be followed by a continuation phase, where those initially randomised to routine care will cross over into the rtCGM intervention for a further 12 weeks. Following this, participants will be invited to join the extension phase of this study and continue rtCGM use for a further 12 months. As such, the expected duration of subject participation is 78 weeks. At least five visits to the study centre and six ‘remote reviews’ are planned for participants over the study duration (see Table 1). During the 12-month extension phase participants will switch from using the Dexcom G6 system to the Dexcom G7 system, once available.

**Table 1 Tab1:** 2GO-CGM study schedule of assessments

	Baseline	Run-in period 14 days	Treatment period week 1–12				Continuation PERIOD Week 12–24			EXTENSION PERIOD Week 25–77			
	Clinic visit		Clinic visit day 1	Remote review week 2, 8	Week 10–12	Clinic visit end of study week 12	Clinic visit week 12	Remote review week 14, 20	Clinic visit end of study week 24	Week 38 remote review	Clinic visit week 51	Week 64 remote review	Clinic visit end of extension study week 77
Informed consent	X								X				
Demographics	X												
HbA1c Height, weight, BMI	X		X			X	X		X		X		X
Medical review	X					X	X		X		X		X
Blood pressure	X					X	X		X		X		X
Urine pregnancy test	X												
Fasting lipids, FBC, glucose, LFTS, eGFR	X					X	X		X		X		X
Urine ACR	X					X	X		X		X		X
Blinded CGM (14 days)		X			X (control arm)								
Return to clinic after 7 days of blinded CGM for new sensor		X			X (control arm)								
CGM training			X				X						
Electronic review				X				X		X		X	
AE collection		X	X	X		X	X	X	X	X	X	X	X
Sleep quality		X				X							
Food diary		X				X					X		

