Qualitative interview						X (CGM arm)			X (control arm)			X (if used both G6 and G7 CGM)	
Retinal scan results	X												

The study protocol was approved by the New Zealand Health and Disability Ethics Committee prior to study commencement (21/CEN/75).

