### Blinded rtCGM

All participants will have at least 10 days of glucose data recorded by blinded Dexcom G6 device in the 2-week run-in phase of the trial. This data will be used by prescribing diabetes nurse specialists (DNS) to maximise non-insulin glucose lowering medications for all participants prior to randomisation into study group.

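### The long-term model does not separate Dexcom G6 from G7, so any systematic difference between them would enter the time trends

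*Protocol article*

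**What the plan says.** Study design in the protocol article sets out the change of device: "During the 12-month extension phase participants will switch from using the Dexcom G6 system to the Dexcom G7 system, once available". No visit or date is fixed for it. Table 1 schedules a late interview marked "X (if used both G6 and G7 CGM"), so the authors allow that some participants may not use both systems.

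Baseline is measured with the older sensor (Blinded rtCGM): "All participants will have at least 10 days of glucose data recorded by blinded Dexcom G6 device".

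Statistical analysis then describes one model for the long-term CGM data: "This data will be pooled with data collected during the run-in and RCT phases and analyses undertaken using linear mixed-effects models". Its purpose is in part to "allow for changes over time to be estimated". The coding is explicit: "Model fixed effects will include current treatment (Dexcom CGM or SMBG), time on study and time on intervention". The random part is described as follows: "Individual variation in glycaemic control at baseline and changes over time will be allowed for using random effects".

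The only comparison of G6 with G7 that the article describes is by interview (Platform Performance; Individual interviews).

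**The concern.** In this trial the CGM is both the treatment and the instrument that measures TIR. A change of generation during the extension is therefore a change of instrument in the period that the model uses to describe the course on longer rtCGM use. The switch goes in one direction and comes late. After week 12 everyone is due to be on rtCGM, so no concurrent SMBG group could show a step that belongs to the sensor.

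The named treatment term has two levels and puts G6 and G7 in the same one. Suppose G7 gives systematically different TIR, because it reads differently or because people use it differently. The named terms that vary during the extension are the two time terms. A step due to the device could then be reported as benefit that fades, or grows, with longer use. A longer series does not average this out, because the step is the same sign for everyone who switches.

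**Working it through.** **The plan's own figure.** The article gives no figure for the long-term model. The sample-size calculation concerns the 12-week comparison and does not bear on this point, except that it supplies a planning TIR of 56% with SD 20 points.

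**Why the time terms take up the shift.** Let G7(t) be 1 after a participant's switch and δ the device difference in TIR points. Leaving δ·G7(t) out of the model adds to each coefficient δ times the coefficient obtained when G7(t) is regressed on the terms that are in the model. In the extension, current treatment equals 1 for everyone. Time on intervention equals time on study in the original rtCGM arm, and time on study minus 12 weeks in the original control arm. Both rise one for one with calendar time, so the trend a reader would see is the sum of the two slopes. G7(t) only goes from 0 to 1, so it is positively related to that sum.

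**How large δ might be (assumption).** The documents give no G6-G7 reading difference. For illustration, take glucose as lognormal with mean 9.5 mmol/L and CV 32%:

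- σ = √ln(1 + 0.32²) = 0.312; μ = ln 9.5 − σ²/2 = 2.203.
- TIR = Φ((ln 10 − μ)/σ) − Φ((ln 3.9 − μ)/σ) = 62.2%.
- Readings 2%, 3% and 5% higher, with true glucose unchanged, give 59.8%, 58.7% and 56.3%: losses of 2.4, 3.5 and 5.9 points.
- At mean 10 mmol/L the same formula gives 56.0%, matching the planning value, and losses of 2.5, 3.7 and 6.1 points.
- This is one average profile. If person means are spread so that TIR averages about 62% with SD about 20 points, the losses fall to about 1.8, 2.7 and 4.5 points.

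A reading difference of 0% gives no loss.

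**How much of δ reaches the trend.** Weekly TIR was simulated for 80 people from week −2 to week 77. Before crossover the control arm had data only at run-in and weeks 10-12. Assumptions: true CGM effect 8 points, no true trend, between-person SD 14, weekly SD 8, no drop-out. A shift of 2 or 5 TIR points was added from the switch onwards. The model had the article's three fixed effects and a random intercept. The entries are the summed time slopes in TIR points per 52 weeks; the truth is 0.

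| Switch pattern | δ = 2 | δ = 5 |
|---|---|---|
| Everyone at week 25, 38, 51 or 64 | 1.5 to 2.4 | 3.1 to 5.6 |
| By calendar date, entry staggered over 52 weeks (16-76% of extension weeks on G7) | 0.8 to 1.8 | 2.0 to 4.4 |

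With no shift, the trend was 0.02. A negative δ gives the mirror image.

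The time terms are not the only place affected. The current-treatment estimate also differed between fits without and with a device term, by at most 1.6 points (6.25 against 7.83; week-51 switch, δ = 5).

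**With a G6/G7 term added.** The apparent trend fell to between −0.6 and +0.7 points per 52 weeks. The estimated shift was 1.8 to 2.6 when the truth was 2, and 4.4 to 5.2 when it was 5, with a standard error of about 0.4.

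These are single runs per scenario, and random slopes were not fitted although the article plans random effects for change over time. They show the mechanism and rough proportion, not a forecast.

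**The case against.** The strongest reply is that this is a condensed article: it says the fixed effects will include three terms, which is not a closed list, and a device covariate could sit in an analysis plan not shown. That may be so. But the article does state how treatment is coded, and that coding merges two devices it plans to use in sequence. The objection lowers the certainty of the point without removing it.

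Several other objections stand and limit the claim:

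- A reader might infer that every remaining participant will switch. The documents do not support this: the switch depends on availability, and Table 1 allows that some may not use both systems.
- A reader might infer that a device artefact will be reported as a change in glycaemic control. No passage says that G6 and G7 read differently.
- If people manage their glucose differently on G7, the change is real. It is still attributable to the device rather than to longer use, but it is not measurement error.
- Laboratory HbA1c at weeks 24, 51 and 77 (Table 1) does not depend on the sensor and would help to expose a spurious TIR step. The article does not connect it to this model.
- The 5- and 10-point thresholds under Binary outcomes are individual improvements from baseline. They are not a yardstick for a mean trend in this model.

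**Conclusion.** The point holds as a conditional one. With G6 and G7 coded as one treatment level, part or most of any systematic difference in measured TIR would be absorbed by the time-on-study and time-on-intervention terms. In the simulations a 2-point shift became 0.8 to 2.4 points per 52 weeks and a 5-point shift 2.0 to 5.6, depending on when people switch. The shift itself is assumed. A 2-5% reading difference corresponds to roughly 2 to 6 TIR points under the lognormal illustration, somewhat less once between-person spread is allowed for, and zero is possible.

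A reader might extend this to the main result, but the documents do not support that. TIR and the hierarchical secondary endpoints are measured in weeks 10-12 or at week 12, before any switch, and the sample size is unaffected. Only the long-term analysis is at issue.

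**What to change.** - Record each participant's G6-to-G7 switch date. The article does not say that this is captured.
- Add a time-varying G6/G7 indicator to the fixed effects of the long-term model, and report its estimate with a confidence interval.
- Repeat the time-trend analysis on G6 data only, censoring each participant at the switch.
- Set the TIR trend beside laboratory HbA1c at weeks 24, 51 and 77. The device term cannot by itself tell a reading difference from a change in behaviour; HbA1c helps with that.

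The cost is one covariate, one sensitivity analysis and wider intervals on the extension trend. How well it works depends on the spread of switch times, which the documents do not give. If most participants switch at a similar study week, the device estimate rests on the assumed shape of the time trend. An early common switch would also cost the G6-only analysis much of the extension data. In that case the report should say that device and duration of use cannot be fully separated, and lean on the HbA1c comparison.

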## Glycaemic and cardiovascular risk management

Participants from all localities will be supported by prescribing DNS based at the Waikato study site, with endocrinologist support if required. For all participants, regardless of randomisation, the prescribing DNS will assist participants to manage dietary and lifestyle factors as well as medications, with a focus on participant self-adjustment of insulin during the RCT and continuation phases. Prescribing DNS will follow an insulin titration algorithm (Appendix) to ensure participants receive standardised insulin adjustment advice based on available glucose data. The prescribing DNS will make medication, diet and lifestyle recommendations (as required) at all clinic visits and remote reviews. Medication recommendations will occur as follows:

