### Run-in phase

During the run-in phase prescribing DNS will adjust non-insulin glucose lowering medications with the aim to maximise these medications prior to the RCT phase for all study participants. DNS will also assess cardiovascular risk factors and adjust anti-hypertensive and lipid lowering medications in the run-in phase and continuation phase, based on national guidelines [34].

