### Randomised controlled trial phase

The RCT phase will be preserved for insulin changes only, unless medication adjustments by DNS are required in this phase for participant safety. For non-urgent cardiovascular risk management during the RCT phase, DNS will request follow up by the participant’s usual care team. Prescribing DNS will provide participants with written insulin titration instructions to follow between scheduled study reviews.

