### Continuation and extension phase

During the continuation and extension phases, prescribing DNS will adjust all glucose lowering and cardiovascular medications if required and provide participants with written insulin titration instructions to follow between scheduled study reviews.

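### The pooled mixed model names no term for the week-12 reopening of non-insulin drug changes, so with linear time, or an abrupt gain, part of a shared drug gain is credited to rtCGM

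*Protocol article*

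**What the plan says.** The drug rules change by phase. In the run-in, the nurses adjust non-insulin glucose-lowering drugs "with the aim to maximise these medications prior to the RCT phase for all study participants" (Run-in phase). After that, "The RCT phase will be preserved for insulin changes only", with an exception for participant safety (Randomised controlled trial phase). In the continuation and extension phases, "prescribing DNS will adjust all glucose lowering and cardiovascular medications if required", with no restriction by arm (Continuation and extension phase). The occasions are frequent: "The prescribing DNS will make medication, diet and lifestyle recommendations (as required) at all clinic visits and remote reviews" (Glycaemic and cardiovascular risk management).

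The crossover falls at the same point. After the 12-week RCT phase, "those initially randomised to routine care will cross over into the rtCGM intervention for a further 12 weeks" (Study design).

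The Statistical analysis section then pools the data from all phases in linear mixed-effects models. It says "These models combine observed between-group and within-person treatment effects", and "Model fixed effects will include current treatment (Dexcom CGM or SMBG), time on study and time on intervention". Random effects cover each person's baseline level and change over time. The form of time on study is not stated, and no phase, period or medication term is named. For the RCT phase the same section says "Real-time CGM data will be collected in the run-in phase and week 10–12 of the RCT phase".

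**The concern.** In the controls, the step from SMBG to rtCGM coincides with the release of non-insulin drug changes. The rtCGM arm gets the same release but no change of device. A model that can represent a common shift at week 12 uses the rtCGM arm to separate the two. A model with only a smooth trend in time cannot bend sharply there. Of the named terms, only current treatment jumps at week 12, so it absorbs part of the shared gain.

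At stake is the only analysis the article states for the continuation and extension CGM data. A reader is likely to take its current-treatment coefficient as the effect of rtCGM. The randomised week 10–12 analysis is not at stake, because it precedes the release.

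**Working it through.** **Timing.** Table 1 gives reviews from week 12 at weeks 12, 14, 20, 24, 38, 51 and 64, before the final visit at week 77. Four of these seven fall in weeks 12–24. The release therefore overlaps the crossover but is not one synchronised step.

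**The protocol's own figures.** It states none for the pooled model. Its sample size figures confirm the variance inputs:

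- Per arm, 2 × (1.960 + 0.842)² × 20² / 14² = 32.0. With the t correction this is 33, as stated (t-test power at 33 is 79.97%).
- The residual SD is 20 × √(1 − 0.58²) = 16.29. Then 10 / (16.29 × √(2/40)) − 1.96 = 0.785, a power of 78.4% against the stated 78%.

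**Inputs.** From the documents: 40 per arm, SD 20 and r = 0.58. These give a between-person variance of 0.58 × 400 = 232 and a residual variance of 400 − 232 = 168. Assumed: weekly TIR means, random-slope variance 0.05 (tried 0 to 0.25), AR(1) residual correlation 0.5 (tried 0 to 0.8), and everyone followed to week 77. Two run-in weeks are on SMBG. Controls contribute weeks 11–12 on SMBG, and both arms are on rtCGM from week 13. The rtCGM arm contributes either all of weeks 1–12 or only weeks 11–12, since the article allows either reading. Results are given in that order.

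**Formula.** The expected coefficient vector is (X′V⁻¹X)⁻¹X′V⁻¹μ. Here X holds the three named effects, V is the covariance above, and μ is a shared one-point gain after week 12 in both arms with no rtCGM effect. The current-treatment element is the share of the gain wrongly credited to it.

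**Linear time, data to week 77:**

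| Shape of the shared gain | Share credited to current treatment |
|---|---|
| Step at week 12 | 0.60 / 0.91 |
| Half at week 12, rest over the six later reviews | 0.31 / 0.47 |
| Equal over the week 12, 14, 20 and 24 reviews | 0.30 / 0.48 |
| 12-week build-up | 0.26 / 0.43 |
| Equal over all seven reviews | 0.10 / 0.16 |

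Over all variance settings the shares run from 0.07 to 0.93. The standard error is 1.16 / 1.29 TIR points.

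**Other smooth forms.**

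- Quadratic time: 0.43 / 0.82 for the step, 0.02 to 0.15 for the 12-week build-up and the week 12–24 reviews, and −0.09 / −0.20 for a 26-week build-up.
- Cubic time, 12-week build-up: −0.04 / −0.08.
- Linear time, data to week 24 only: 0.33 / 0.74 for the step, −0.05 / −0.15 for the 12-week build-up.

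A separate calculation with other variance assumptions, which also tried 70% entering the extension, agrees. Under linear time it gave 0.64–0.93 for a step and 0.35–0.57 for a 12-week build-up. Under quadratic, cubic, spline and log time the share of a step was always positive (0.06–0.82), while gradual gains ranged from −0.31 to +0.38.

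**With the week-12 shift represented, data to week 77:**

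| Model | Share | Standard error |
|---|---|---|
| Linear time plus a term for weeks 13 onward | −0.04 to 0.06 | 1.34 / 1.98 |
| Time by phase | −0.11 to 0.00 | 1.95 to 2.33 (both categorical forms) |
| Time by week | 0.00 | as above |

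**Scale, for illustration.** The documents give no size for the drug gain. If it were 3 TIR points, linear time would give a bias of 3 × 0.10 = 0.3 to 3 × 0.16 = 0.5 points when spread over all seven reviews. It would give 0.9 to 1.4 over the week 12–24 reviews, and 1.8 to 2.7 for a step.

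**The case against.** **The form of time is left open.** The model sentence need not be a closed list, and an analysis plan could enter time by week or add a period term, which would remove most or all of the leak. This stands as a limit, so the point is conditional. It remains a point because the article does name the fixed effects, and its own drug rules create the overlap that those effects do not mark.

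**A reader might infer that any smooth time curve inflates the rtCGM effect.** The calculations do not support that. Slow gains leak little, or with reversed sign, under flexible curves, and also under linear time when only data to week 24 are used.

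**A reader might infer a bias near 2.7 points.** That needs a synchronised step, the sparser reading of the RCT data and an assumed 3-point gain. The review schedule spreads the changes, run-in optimisation limits what is left to change, and later changes are made only if required.

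**The remedy costs precision.** Suppose half of both arms change drugs, each change worth an assumed 6 points, with changes front-loaded at week 12. Linear time has bias 0.83 / 1.24, hence root mean square error √(0.83² + 1.16²) = 1.43 and √(1.24² + 1.29²) = 1.79. With the phase term, bias is −0.04 / −0.05 and the error is about 1.34 / 1.98. The remedy is slightly better on the first reading of the data and worse on the second. This stands: the gain is in validity, not always in total error.

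**A common term does not cover changes that differ by arm.** This is true. If only controls gain, +0.10 to +0.48 of the gain remains; if only the rtCGM arm gains, −0.12 to −0.48. Adjusting for drug changes or censoring at them is not clearly right either, because changes prompted by rtCGM data may be part of its effect under this model of care.

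**A reader might see a conflict with the Appendix**, which keeps non-insulin therapies going throughout the study. There is none: that note concerns stopping drugs, not adding them.

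**Conclusion.** The point holds in conditional form. The drug release and the controls' switch share week 12, and the pooled model as described marks only the switch. With linear time over 77 weeks, about 0.1 to 0.5 of a shared gain spread over the reviews is credited to current treatment, and 0.6 to 0.9 of a step. A step also leaks under every other smooth form tried. A slow gain under flexible curves may leak little or with reversed sign, and with time by week the leak is zero.

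These shares rest on the protocol's SD and correlation and on assumed slope variance, autocorrelation and gain shapes. The absolute bias cannot be stated, because the documents do not say how much drug change will remain after the run-in. The primary and ordered secondary results are untouched. The matter is worth correcting in the secondary model and does not threaten the trial's main conclusion.

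**What to change.** Leave the drug rules as they are. In the Statistical analysis section, state the form of time on study and enter it by week or by phase. If time is kept linear, add a fixed effect for weeks 13 onward that is common to both arms. Week categories are the safest choice: in a check, quadratic time plus the week-13 term still left −0.16 of a 12-week build-up. State that the week-12 randomised comparison estimates the rtCGM effect and that the pooled model describes the later course.

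The cost is precision, with no change to care. The standard error rises from about 1.2–1.3 TIR points to 1.3–2.0 with the added term, and to as much as 2.3 with week categories. Precision given up this way came from assuming no common shift at week 12.

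A sensitivity analysis that adjusts for non-insulin drug changes is at most optional. It would require the dates of changes to be recorded at reviews, and it answers a different question if rtCGM data prompted the changes.

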### Sample size and power calculation

In a recent study examining intermittent CGM in a population with type 2 diabetes, baseline time in range (TIR) was 62.5% ± 20% [32]. Our inclusion criteria predicts a population that are likely to have lower time in range, which we estimate at 56% ± 20%. To detect a difference to a mean improvement of 14% TIR (to the target TIR of 70% set by international guidelines), at 80% power and α of 0.05, we would need 33 participants in each arm. The sample size has been inflated to 40 participants in each arm to account for possible loss-to-follow-up. This power calculation is a conservative estimate, and we are likely to be able to detect a smaller difference. For example, adjusted for baseline TIR a sample size of 40 per group will give 78% power to detect a difference of 10% TIR, assuming a within-person standard deviation of 18.5% (correlation coefficient of r = 0.58) [32], and that there is no loss-to-follow-up. The mean between-group difference in TIR at 12 weeks will be estimated with 95% confidence intervals using analysis of covariance, a general linear model that adjusts for TIR at baseline.

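### Fitted as it naturally reads, the pooled mixed model on daily CGM data leaves serial correlation unmodelled, so its standard errors for the rtCGM effect would be about 2 to 3 times too small

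*Protocol article*

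**What the plan says.** All references are to the protocol article. The last paragraph of Statistical analysis states that "Real-time CGM data will be collected daily during the entire continuation and extension study phases" and that "This data will be pooled with data collected during the run-in and RCT phases and analyses undertaken using linear mixed-effects models". The systematic part is given: "Model fixed effects will include current treatment (Dexcom CGM or SMBG), time on study and time on intervention". Within-person dependence is covered by one sentence: "Individual variation in glycaemic control at baseline and changes over time will be allowed for using random effects". The models are meant to use both sources of contrast: "These models combine observed between-group and within-person treatment effects, and allow for changes over time to be estimated".

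The paragraph does not say whether the response is a daily value or a period summary. It does not name a residual covariance or a robust variance. The general rule earlier in the section is "Two-sided P-values will be reported, with an alpha of 0.05 considered statistically significant".

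The primary analysis is separate. It is described as "fitting an ordinary least squares linear regression model with percentage time in target glucose range at 12 weeks as the dependent variable", with one value per participant.

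**The concern.** A random intercept and slope make a participant's days independent once that person's level and straight-line trend are known. Glucose control also drifts over days and weeks with illness, diet, adherence and titration steps, and neighbouring days share that drift.

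The design makes this costly. The SMBG condition is seen by CGM in only one 14-day window for the rtCGM arm (run-in) and two for the control arm (run-in and weeks 10–12). Against this stand up to 14 + 84 + 364 = 462 rtCGM days per person. A participant's drift during a short SMBG window would count as about 14 separate observations rather than nearly one.

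At stake are the p-values and intervals for current treatment and time on intervention in the long-term CGM results. The paragraph gives no other analysis for those pooled CGM data.

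**Working it through.** **1. Reproduce the plan's figures (Sample size and power calculation).**
- n per arm for 14 points, SD 20, 80% power: 2 × (1.96 + 0.84)² × (20/14)² ≈ 32.04, rounded up to 33, as stated.
- ANCOVA residual SD: 20 × √(1 − 0.58²) = 16.29. With 40 per arm and 10 points, power is 78.4%; the plan states 78%.
- SD of change: 20 × √(2 × (1 − 0.58)) = 18.3, against "assuming a within-person standard deviation of 18.5% (correlation coefficient of r = 0.58".

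So the 78% figure uses r = 0.58 as the correlation between baseline and 12-week TIR, each measured over two weeks.

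**2. What r = 0.58 implies.**
- Non-persistent variance of a 2-week mean: 400 × (1 − 0.58) = 168, an SD of 13.0 points.
- Fourteen independent days with an assumed daily SD of 15 would give 15/√14 = 4.0 points.
- For independent daily noise alone to give 13.0, the daily SD would have to be √(168 × 14) = 48.5. The ceiling for a 0–100% measure with mean 56 is √(56 × 44) = 49.6.
- For straight personal trends alone, 18.3 points over 12 weeks becomes 18.3 × 77/12 ≈ 118 points over 77 weeks, which is impossible on this scale.
- Mixing the two with daily SD 25: noise contributes 2 × 625/14 = 89 of the change variance of 336. The remaining 247 is an SD of 15.7 over 12 weeks, or about 101 points over 77 weeks.

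Neither component, nor this mixture, plausibly yields r = 0.58. Some drift shared by neighbouring days is implied.

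**3. Simulation with no rtCGM effect.** There were 40 participants per arm with 14 run-in days, 14 days at weeks 10–12, 84 continuation days and 364 extension days. The fixed effects were those planned, with a random intercept and slope, independent residuals, REML and a two-sided 0.05 test of current treatment. Daily noise, drift time constants and complete data are assumptions.

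Drift matched to SD 20 and r = 0.58, daily noise SD 12 (500 runs; 800 for 14-day means):

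| Drift time constant | Model SE | True SD of estimate | Ratio | Rejection, daily | Daily, clustered SE | 14-day means | 14-day means, clustered SE |
|---|---|---|---|---|---|---|---|
| 7 days | 0.69 | 1.72 | 2.5 | 44.6% | 5.2% | 5.9% | 5.0% |
| 14 days | 0.63 | 1.67 | 2.7 | 46.0% | 4.4% | 8.8% | 6.6% |
| 30 days | 0.59 | 1.79 | 3.1 | 50.0% | 6.6% | 12.0% | 6.3% |

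With daily noise SD 15–25 and time constants of 7–28 days, rejection is 27–53%. The model SE is then 0.67–0.94 against a true SD of 1.6–2.0.

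Uncalibrated AR(1) residuals, SD 15 (500 runs):

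| Lag-1 correlation | 0 | 0.1 | 0.2 | 0.3 | 0.5 | 0.7 | 0.9 |
|---|---|---|---|---|---|---|---|
| RCT data from weeks 10–12 only | 5.4% | 7.2% | 9.4% | 14.0% | 23.2% | 39.2% | 53.4% |
| All RCT days in the rtCGM arm | 4.6% | 9.0% | 10.6% | 13.6% | 20.6% | 37.2% | 52.2% |

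The level holds when days really are independent, so the inflation comes from the unmodelled correlation and not from the code.

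**The case against.** The strongest reply is that the paragraph fixes none of the three conditions behind the large figures.

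- **Response unit.** Daily collection describes device wear. The only CGM metric the article defines is one value per participant per window. With 2-week summaries the rate is about 4–14%. This stands, though that range still reaches well above 5%.
- **Form of the random effects.** Change over time need not mean a straight line. With drift constants of 7, 14 and 28 days, adding a participant-by-phase random intercept to daily data gave 5%, 7% and 10%. A participant-by-fortnight intercept gave 5%, 6% and 12% (150 runs per cell, so about ±4–5 points). This stands too: the size depends heavily on that choice.
- **Residuals.** A condensed article may leave the covariance to the full protocol or SAP. That is fair as to silence. But the paragraph does say how within-person variation is to be handled, and its natural reading conflicts with the r = 0.58 used for power.
- **Calibration.** The cited source of r is not at hand, and its window and interval are not stated. The plan's own 78% does use r as the baseline to 12-week correlation, but daily noise and drift constants remain assumptions.

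A reader might infer that the plan specifies independent residuals, or that the trial's main conclusion is exposed to a false-positive rate near 50%. The document supports neither. It does not state independence. The primary TIR test and the ordered secondary tests use one value per participant, and the pooled model carries no named confirmatory hypothesis.

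**Conclusion.** The point holds conditionally and is confined to the supplementary pooled longitudinal model. Given daily values, a random intercept and slope, and independent residuals, the standard error for current treatment is too small by a factor of about 2–3, and a true null is rejected in roughly 27–53% of trials. That rests on the calibration to SD 20 and r = 0.58, daily noise SD 15–25 and time constants of 7–28 days. Weak AR(1) correlation of 0.1–0.2 gives about 7–11%. This is more than missing detail, because an analyst who follows the paragraph as it naturally reads would get wrong error bars. The change should be made, but the trial's main conclusion does not depend on it.

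**What to change.** In the last paragraph of Statistical analysis, keep the planned fixed and random effects and make these changes:

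1. State the response unit, preferably 2-week summaries of each CGM metric. Summaries alone are not sufficient.
2. Base tests and intervals for current treatment and time on intervention on participant-clustered robust standard errors, or on a serially correlated within-person residual (AR(1) or continuous-time exponential).

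Clustered standard errors gave about 3–9% on daily data and about 4–7% on 2-week means across the scenarios run. An AR(1) residual gave 1.7–5.8%, but with only 120 runs per cell and on data that were truly AR(1). If the serial residual is chosen for daily values, it should allow independent day noise alongside the drift.

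The cost is a sentence or two of plan text and a few lines of R or Stata. No new data are needed. The long-term intervals will be wider.
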